### Randomization and allocation

As this was a multicenter trial, stratified block randomization, with the institution as a stratification factor, will be used to randomly allocate the participants to the experimental and control groups. Randomization will be performed using the SAS 9.4 statistical software (SAS Institute Inc., Cary, NC, USA). A statistician will generate randomization codes, assign serial numbers to all 184 participants, and randomly allocate them to the two groups in a 1:1 ratio to ensure reproducibility. The codes assigned to the participants through randomization will be stored in a double-locked cabinet.

If a participant is deemed eligible after the screening procedure, the investigators will open an opaque allocation envelope containing a piece of paper labeled “experimental group” or “control group” in front of the participant. The investigators will subsequently inform the participants of the allocation results and assigned intervention. Envelopes will be stored separately.

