## Methods

### Study setting

This multicenter, participant-assessor-blinded, sham-controlled trial will be conducted at two hospitals affiliated with Dongshin University: Naju Dongshin University Korean Medicine Hospital and Dongshin University Mokpo Korean Medicine Hospital, Korea. The trial has been registered with theregistered with the Clinical Research Information Service of the Republic of Korea (registration no. KCT0009870).

At the time of writing this report, enrollmenthas not started. Participant recruitment will take place from January 10, 2025, to January 10, 2026.

The present protocol satisfied the Declaration of Helsinki and was conducted following CONSORT reporting guidelines [9]. Written informed consent was obtained from each participant before registration. A flowchart of the study is shown in Fig. 1.

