#### Exclusion criteria

Patients meeting any of the following criteria will be excluded:

Patients with severe skin diseases other than AD or severe oozing and maceration of the atopic lesions, who may affect the results of this study in the investigators’ opinion.Patients with skin diseases due to other internal (e.g., liver diseases, renal failure), psychotic, or neurological conditions that are expected to affect the results of this study.Patients who have used systemic medications, including corticosteroids, antibiotics, immunosuppressants/immunomodulators (systemic corticosteroids, cyclosporine, mycophenolate mofetil, interferon-gamma) within 1 month before the screening visit. Exceptionally, the administration of systemic antihistamines was allowed during the trial within the dose at the randomization visit if they had been administered at a constant dose for 1 month before randomization. Reduction and discontinuation were permitted, but an increase was prohibited.Other severe comorbidities (e.g., heart diseases, kidney diseases, liver diseases, respiratory diseases, malignancy, immunodeficiency, etc.) deemed inadequate by the principal investigator. The abnormality criteria for liver function is defined as aspartate transaminase (AST) or alanine transaminase (ALT) level five times higher than the upper limit of the analyzed institution, and those for renal function is defined as three times higher than the upper limit of the analyzed institution.Severe or uncontrolled asthma (exacerbation of asthma requiring systemic corticosteroids for at least attacks of 3 days more than two times per year)Allergy to adhesives.Pregnant, lactating women, or women planning pregnancy.Patients deemed unsuitable by the principal investigator.

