### Sample size

In our previous study, the mean changes in the O-SCORAD score for 4 weeks were 9.2 ± 3.73 and 7.2 ± 3.91 in the BMA-AD and IDA-AD groups, respectively. Based on these results, we will conservatively evaluate the changes for 4 weeks in the BMA and sham devices. The number of participants required for this study was calculated as follows:$${n}_{1}=\frac{{2({Z}_{\alpha/2}+{Z}_{\beta})}^{2}{\sigma}^{2}}{{\left(\mu1-{\mu}_{2}\right)}^{2}}=64$$

The required sample size was determined to be 64 cases per group (‘experimental group’ and ‘control group’).$$N=\frac{{n}_{1}}{1-r}\cong92$$

Assuming a 30% drop out rate of participants at follow-up, we calculated the sample size to be 92 cases for each group and a total of 184 participants for both groups.

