### Blinding

Participants and outcome assessors will be blinded to the treatment group allocations. It is not possible to blind the physician; therefore, the Korean medicine doctor (KMD) who will perform the treatment will not participate in the trial outcome assessment or data collection and analysis.

Each hospital will designate several KMD trained to perform the therapy and obtain relevant operational qualifications.

The outcomes will be assessed before and after the intervention. To ensure blinding, we will choose a sham device as a placebo control in this participant-assessor-blinded clinical trial and use eye masks to shield the participants’ eyes.

The treatment device will be of the same size and material, and the treatment method will maintain a consistent frequency and intensity.

In case of serious AEs, the principal investigators at each participating center will decide whether allocation concealment needs to be broken. If allocation concealment is broken before the end of the trial, the data will be censored from the analysis and the patients will be considered to have dropped out of the trial.

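### Investigators, the role that also applies discretionary eligibility criteria, open labelled envelopes under site-stratified blocks, and the article does not separate envelope opening from enrolment

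*Protocol article*

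**What the plan says.** All references are to the Protocol article.

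- **Randomization and allocation** gives the method: "stratified block randomization, with the institution as a stratification factor, will be used". A statistician generates the list in SAS for all 184 participants, to "randomly allocate them to the two groups in a 1:1 ratio".
- **Study setting**: the trial "will be conducted at two hospitals affiliated with Dongshin University", so there are two strata.
- **Randomization and allocation** also says who reveals the assignment and when: "If a participant is deemed eligible after the screening procedure, the investigators will open an opaque allocation envelope", the envelope "containing a piece of paper labeled “experimental group” or “control group” in front of the participant". The next sentence has the investigators tell participants their allocation.
- The same section states safeguards: the codes are kept in a double-locked cabinet and the envelopes are stored apart.
- **Exclusion criteria** contain judgement calls. One turns on the investigators' opinion of whether other skin disease would affect the results. The last is open-ended: "Patients deemed unsuitable by the principal investigator".
- **Blinding** has a separation rule for the treating doctor: "the Korean medicine doctor (KMD) who will perform the treatment will not participate in the trial outcome assessment or data collection and analysis". It concerns what follows randomisation, not screening or enrolment.

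**The concern.** An opaque envelope hides the next slip. It does not hide the tally of slips already opened. In a permuted block that tally carries information, because the arm that is behind must catch up before the block ends. With separate blocks in each of two hospitals, the relevant tally is the local one, which site staff are best placed to follow.

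The article gives the task of opening envelopes to the same role, the investigators, that applies the discretionary exclusions. If people involved in enrolment know past assignments, they can form a better-than-chance expectation of the next arm before deciding whether a borderline patient is suitable. Patients with a better or worse outlook could then be admitted, deferred or declined according to the expected arm.

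That would bias the BMA-minus-sham difference in O-SCORAD change. The sham device and blinded assessor cannot correct it, because the groups would already differ in prognosis at entry.

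**Working it through.** The article gives no predictability figure to reproduce and no block size. The absence of a block size from an article is no fault, so it is treated as an assumption and a range is shown.

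**Inputs from the article**
- 1:1 allocation, blocks within two hospitals (Randomization and allocation; Study setting).
- 92 per group: "we calculated the sample size to be 92 cases for each group and a total of 184 participants for both groups" (Sample size).
- Pilot SDs of 4-week O-SCORAD change of 3.73 and 3.91; pilot means 9.2 and 7.2, a difference of 2.0 (Sample size). The pilot comparator was intradermal acupuncture, not sham, so these serve only as a scale.

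**Assumptions**
- Fixed block sizes of 2 to 10 known to the guesser, or varying sizes unknown to the guesser.
- The guesser sees all earlier assignments at the site, names the arm that is behind, and tosses a coin when the arms are level.
- For the bias illustration only: every enrolment is steered, and patients admitted when BMA is expected improve by η points more than those admitted when sham is expected.

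**Step 1: predictability, block of 4 by hand.** The chance of a correct guess at positions 1 to 4 is 1/2, 2/3, 2/3 and 1.
- Correct guesses: (0.500 + 0.667 + 0.667 + 1) / 4 = 2.833 / 4 = 0.708.
- Certain in advance: position 3 in one third of blocks, and position 4 always: (0.333 + 1) / 4 = 0.333.

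Enumerating every block for the other sizes gives:

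| Fixed block size | Correct guesses, c | Certain in advance |
|---|---|---|
| 2 | 75.0% | 50% |
| 4 | 70.8% | 33% |
| 6 | 68.3% | 25% |
| 8 | 66.6% | 20% |
| 10 | 65.3% | 17% |

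With sizes varied at random and unknown to the guesser (simulation, 4,000 runs, 92 patients at a site as an assumed even split), correct guesses are 69% for sizes 4/6, 68% for 4/6/8 and 70% for 2/4/6. Certainty then largely disappears, but predictability does not. Without sight of earlier slips the figure is 50%.

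**Step 2: bias if the knowledge were fully used.** A share c of the BMA group and 1 − c of the sham group would have entered when BMA was expected. The bias is therefore (c − (1 − c)) × η = (2c − 1) × η.

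**Step 3: type I error.**
- Pooled SD = √((3.73² + 3.91²) / 2) = 3.82.
- SE = 3.82 × √(2/92) = 0.563.
- Type I error = P(|Z + bias/SE| > 1.96).

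| Block size | Bias, η = 1 | Bias/SE | Type I error, η = 1 | Type I error, η = 0.5 |
|---|---|---|---|---|
| 2 | 0.50 | 0.89 | 14.4% | 7.3% |
| 4 | 0.42 | 0.74 | 11.5% | 6.6% |
| 6 | 0.37 | 0.65 | 10.0% | 6.2% |
| 8 | 0.33 | 0.59 | 9.1% | 6.0% |

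At η = 1 and blocks of 4, the bias of 0.42 is 21% of the 2.0-point pilot difference.

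**The case against.** The strongest reply is that the article does not say what a reader may take from it.

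- **Same people?** A reader might infer that the individuals who screen also open every envelope and so see the whole sequence at their hospital. The eligibility clause is in the passive and the investigators are named collectively, so this is an inference from a shared role, not a statement. The Blinding section also has each centre's principal investigator decide, after a serious adverse event, whether to break concealment, which suggests that this role does not normally know the allocation. If the independent outcome researcher also scores the screening O-SCORAD, the 10–40 entry criterion would be in blinded hands.
- **Certain prediction?** A reader might infer that upcoming assignments can simply be read off. That needs a known block size, and even with known blocks of 4 two thirds of assignments remain uncertain. Undisclosed, varying blocks may already be specified in the full protocol.
- **Stated safeguards.** A statistician's list, locked codes, separately stored opaque envelopes and opening only after eligibility are real protections and deserve credit.
- **Size.** The type I error figures need an assumed prognostic shift and steering at every enrolment. Nothing in the article supports either.

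All four points limit the claim, but none removes it. The safeguards cover unopened slips and the current decision; they do not cover what is learned from slips already opened. Varying the block sizes leaves correct guesses at 68% to 70%. The hint about the principal investigator does not extend to other investigators, and it sits uneasily with the sentence that has the investigators announce the allocation.

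**Conclusion.** The point holds in a conditional form. The article has the role that applies discretionary eligibility criteria open plainly labelled envelopes under site-stratified blocks, and it does not separate that act from enrolment. Investigators involved in enrolment who see earlier slips could guess the next better than chance: about 65% to 75% over assumed fixed blocks of 10 to 2, and 68% to 70% with unknown varying sizes.

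The documents do not establish that the same individuals do both tasks, that anyone can predict with certainty, or that the trial's type I error will be any particular figure. The 9% to 14% range (6% to 7% for a half-point shift) shows what is at stake if the route were fully used; it is not a forecast. The procedure is worth changing because it is a stated one, the exposure is avoidable and the remedy is cheap.

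**What to change.** In Randomization and allocation, replace the envelope procedure with wording to this effect:

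> Once eligibility and enrolment have been irrevocably recorded, a treating KMD who takes no part in screening at that site opens the next sequentially numbered, sealed envelope for the site, away from the participant (or receives the code from the statistician). Screening investigators and outcome assessors are not told the allocation.

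The neighbouring text must change with it. Opening the labelled slip in the participant's presence and having the investigators announce the allocation contradict both this wording and the participant blinding in the Blinding section. The announcement conflict is a separate defect, and curing it alone would not cure this one.

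As a secondary step, and only if not already planned, vary the block sizes within institution and do not disclose them to the sites. This removes most certainty but little predictability, so it cannot replace the change in who opens the envelope.

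**Cost.** Mainly protocol wording, plus a revised list if block sizes change. The treating KMDs are already unblinded, but the article does not say whether any of them also screens, so each hospital must confirm that a non-screening KMD is available at randomisation. Varying blocks may allow slightly more imbalance at the end of recruitment.

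**Timing.** The article says enrolment had not begun at the time of writing, but recruitment was planned to end on January 10, 2026, and publication is dated 2026-03-09. If patients have already been randomised, the sponsor should report who screened, who opened envelopes and what block sizes were used, so that readers can judge the risk of selection bias.

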**Fig. 3 Fig3:**
[figure not shown]
Comparison of sham and biodegradable microneedle acupuncture (BMA) Patches This figure illustrates the sham and BMA patches utilized in the research. The upper section depicts the external packaging of both patches, which are designed to be indistinguishable to maintain blinding. The central section reveals the internal product, featuring a circular patch with a clear protective layer. The lower section emphasizes a significant distinction: the sham patch is devoid of microneedles, whereas the BMA patch is equipped with biodegradable microneedles on its surface

All the treatments will be administered by a KMD with more than 1 year of clinical experience in Korean medicine dermatology. The KMD will have undergone more than 10 h of training and simulation to ensure that they are able to provide identical acupuncture treatment in accordance with the predefined protocol.

A total of 184 participants with indications for the 10 acupoints (PC6, LI4, LI11, ST36, and SP10, bilaterally) (Fig. 4) will be randomly assigned to the BMA or sham device treatment groups in a 1:1 ratio. The assigned participants will be treated with BMA or a sham device.

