**Fig. 4 Fig4:**
[figure not shown]
Locations of acupoints for biodegradable microneedle acupuncture (BMA) Treatment This figure depicts the five acupoints utilized in the study for BMA treatment. The chosen acupoints are LI11 (Quchi), LI4 (Hegu), PC6 (Neiguan), ST36 (Zusanli), and SP10 (Xuehai). These points are strategically positioned on the arms and legs and are frequently employed in traditional Korean medicine to manage inflammation, modulate the immune system, and treat skin-related issues. The application of BMA at these specific points is intended to amplify the therapeutic effects for symptoms associated with atopic dermatitis (AD)

For 4 weeks, treatments will be performed three times a week for a total of 12 times.

The investigators will instruct the participants on how to remove the BMA and disinfect the treated area themselves 4 h after treatment. The investigators will distribute Medical Device Removal Time record diaries to the participants at each visit and instruct them on the removal time record sheets.

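### The allocation procedure has each participant told their arm, which contradicts the participant blinding stated in the rest of the protocol article

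*Protocol article*

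**What the plan says.** The protocol article gives two accounts of what the participant knows.

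- **Randomization and allocation.** Once a participant is found eligible, "the investigators will open an opaque allocation envelope containing a piece of paper labeled “experimental group” or “control group” in front of the participant". The next sentence reads: "The investigators will subsequently inform the participants of the allocation results and assigned intervention".
- **Blinding.** "Participants and outcome assessors will be blinded to the treatment group allocations". The means are given as follows: "we will choose a sham device as a placebo control in this participant-assessor-blinded clinical trial and use eye masks". Only the treating Korean medicine doctor is described as impossible to blind, and that doctor is kept out of outcome assessment, data collection and analysis.
- **Fig. 3 legend.** The outer packages of the two patches are described as ones "which are designed to be indistinguishable to maintain blinding".
- **Abstract (Methods) and Study setting.** Both describe the trial as blinded for participants and assessors.

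**The concern.** A participant who has seen the group label and been told which intervention they will get is not blinded, whatever is done afterwards. The sham patch, matched packaging and eye masks all exist to withhold one piece of information, and the allocation procedure hands that information over before any of them comes into use.

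At stake is the purpose of the sham arm, which is to make expectation equal in the two groups. If participants know their arm, a difference in self-reported itch, symptoms or quality of life mixes the effect of the microneedles with the effect of knowing one did or did not receive them.

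**Working it through.** The article states no figure on this point, so the check is a comparison of the sections.

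1. **Timing.** The envelope is opened after eligibility is confirmed and in order to assign treatment. Disclosure therefore comes before the first of the 12 treatment sessions.
2. **Content.** The slip carries the group name, not a code, and the participant is told the assigned intervention as well as the allocation result.
3. **Possible limits.** I looked for wording that would confine the disclosure to a code, delay it until the end of the trial, or restrict it to the treating doctor. The article has none.
4. **Can the masking measures compensate?** Identical packaging and eye masks stop the participant from seeing a difference, and the sham patch stands in for the real one. None of them works against a label the participant has read or a statement they have been given.
5. **Number affected.** The procedure applies to everyone randomised: 92 + 92 = 184.
6. **Outcomes directly exposed.** The participant marks the pruritus VAS. POEM, DLQI and EQ-5D-5L also rest on the participant's own answers, and the QALYs in the economic evaluation are computed from EQ-5D-5L.
7. **Outcomes indirectly exposed.** Under Primary outcome measure, an independent researcher evaluates the outcomes, and O-SCORAD leaves out itch and sleep disturbance. Nothing in the allocation section says the assessor is told the arm. Two routes remain open:
   - The participant may reveal the arm to the assessor. This also applies to EASI.
   - Knowledge of the arm may affect use of rescue cream, which is available for severe pruritus in consultation with the investigators, or withdrawal, since unsatisfactory effect is a listed reason for discontinuation. The sample size allows for 30% dropout (64 / 0.70 = 91.4, rounded up to 92 per group), and missing values are filled by last observation carried forward, so any difference in withdrawal between arms would enter the primary analysis.

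The article contains nothing from which the size of either route could be estimated.

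**The case against.** The strongest reply is that the allocation paragraph is a drafting slip, perhaps wording kept from an open-label design. Every other relevant part of the article describes participant blinding, so sites may well follow the Blinding section. That stands to this extent: the article cannot show which instruction is followed, and a reader who infers that the trial is, or was, open-label goes beyond it. It does not remove the contradiction, because the article nowhere identifies the paragraph as a slip. Nor can the conflict be put down to a condensed article. This is not an omitted detail but a positive instruction that conflicts with another.

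A second reply is that the primary outcome is rated by an independent assessor and excludes the subjective items. That also stands, and it is why the direct risk is confined here to self-reported outcomes, none of which is primary.

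Four stronger readings are tempting, but the article does not support them:

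- **Patch removal as a second leak.** Fig. 3 says "the sham patch is devoid of microneedles, whereas the BMA patch is equipped with biodegradable microneedles on its surface", and the investigators are to "instruct the participants on how to remove the BMA and disinfect the treated area themselves" 4 h after treatment. However, each participant receives only one type of patch, the needles are biodegradable, and the article does not say what is still visible at removal.
- **A bias worth half the target effect.** This needs an assumed 1-point shift in O-SCORAD set against a 2.0-point difference (9.2 − 7.2). The article gives no basis for the 1 point. The 7.2 is the change with intradermal acupuncture, an active treatment, in the earlier study and not a sham response. The Sample size section does not state which difference entered its formula.
- **Censoring of every participant.** The Blinding section says: "If allocation concealment is broken before the end of the trial, the data will be censored from the analysis". That sentence directly follows the rule on breaking concealment after serious adverse events, and stretching it to routine allocation takes it out of context.
- **Loss of the sham comparison.** With disclosure the control would still be a sham, but an unblinded one.

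**Conclusion.** The contradiction is real and should be corrected. If the allocation procedure is carried out as written, all 184 participants know their arm before the first treatment, and the self-reported outcomes (pruritus VAS, POEM, DLQI, EQ-5D-5L and the QALYs) are directly open to expectation bias. For O-SCORAD the risk is indirect and of unknown size, and arm-dependent rescue use or withdrawal is a possibility rather than an established consequence. The contradiction itself rests on no assumption beyond the plain meaning of the two sections. The consequences depend on sites following the allocation paragraph rather than the Blinding section.

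**What to change.** Bring Randomization and allocation into line with Blinding:

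- Delete the opening of the envelope in the participant's presence and the sentence on informing participants.
- Replace the group name on the slip with a coded kit number, which the matched outer packaging already allows.
- Have the treating doctor open the envelope out of sight of the participant and the outcome assessor. This doctor is already unblinded and already excluded from assessment.

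The cost is one rewritten paragraph, a matching site instruction and relabelled envelopes. No new unblinded role is created.

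This may no longer be possible prospectively. Study setting says enrolment had not begun at the time of writing, but it gives a recruitment window ending January 10, 2026, and the article is dated 2026-03-09. If recruitment has run, the sponsor should state what participants were actually told. If they were told their arm, the trial should not be described as participant-blinded, and the self-reported results should be read accordingly.

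A question at Visit 13 asking participants to guess their arm would be a useful optional addition. Its absence from the article is not part of this finding.
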